#### Secondary objectives

To evaluate whether TB alone reduces overdetection of clinically insignificant PCa (ISUP 1) compared with TB + SB.To compare patient-reported outcomes (EPIC‑26, EORTC‑QLQ‑C30, VAS) between arms.To assess complication rates, biopsy avoidance due to mpMRI triage, biopsy approach (transrectal vs transperineal), MR in-bore biopsy yield, ISUP ≥ 3 cancers, stability of PI-RADS on follow-up MRI, and bpMRI vs mpMRI performance.To validate AI and radiomics models for PCa detection.

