#### Prostate biopsy

MRI/US fusion targeted biopsies (TB) and systematic 12-core biopsies (SB) will be performed via transrectal or transperineal access under local or general anesthesia. TB consists of 4 targeted cores per lesion (up to 3 lesions). Participating urologists must demonstrate certification and ≥ 100 lifetime fusion biopsies, following a standardized QA protocol. Implementation adherence will be monitored as detailed in the quality handbook.

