#### Secondary outcomes

Patient-reported outcomes (EPIC-26, EORTC-QLQ-C30, VAS)

Measured using validated questionnaires (metric: continuous scores), analyzed as mean changes over time and between groups (aggregation: mean differences), assessed at baseline, 30 days, and 12 months.Biopsy-related complications

Defined as adverse events within 30 days post-biopsy (measure: clinical assessment; metric: categorical/binary), summarized as proportions by study arm, assessed at 30 days post-procedure.Biopsy avoidance due to mpMRI triage

Defined as the proportion of participants not undergoing biopsy due to non-suspicious mpMRI findings (PI-RADS 1–2 or PI-RADS 3 with PSAD ≤ 0.15), reported as proportion, assessed at screening.Diagnostic performance of DRE

Defined as the association between DRE findings and biopsy outcomes (metric: sensitivity, specificity), analyzed cross-sectionally at baseline and biopsy.Biopsy approach (transrectal vs. transperineal)

Compared in terms of pain (VAS score) and infection rates (binary), summarized as mean differences and proportions, assessed within 30 days post-biopsy.MR in-bore biopsy yield

Defined as detection of csPCa in participants undergoing MR in-bore biopsy after negative or ISUP 1 results (metric: binary), reported as proportion, assessed within 3 months post-biopsy.Detection of higher-grade cancer (ISUP ≥ 3)

Defined as presence of ISUP ≥ 3 cancer on histopathology (metric: binary), reported as proportion, assessed at index biopsy.Comparison of bpMRI vs mpMRI

Retrospective comparison of detection performance (metric: paired binary outcomes), analyzed using constrained maximum likelihood methods, assessed at baseline imaging.Change in PI-RADS score

Defined as change in PI-RADS category between baseline and follow-up MRI (metric: ordinal change), reported as proportions of up- or downgrading, assessed at 12 months.Index-lesion-only analysis

Detection of csPCa based on index lesion targeting only (metric: binary), reported as proportion, assessed at index biopsy.AI and radiomics validation

Diagnostic performance of AI-based models (metric: AUC, sensitivity, specificity), analyzed retrospectively, assessed using baseline imaging and biopsy outcomes.

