## Assignment of interventions: allocation

### Sequence generation {16a}

Participants will be randomized in a 1:1 allocation ratio to either Arm A (targeted biopsy only) or Arm B (targeted + systematic biopsy). Randomization will use computer-generated permuted blocks of variable size and will be stratified by study center to ensure balance across recruitment sites.

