## Assignment of interventions: blinding

### Who will be blinded {17a}

Clinical teams cannot be blinded due to procedural differences between study arms. Radiological assessment (including PI-RADS scoring) is performed prior to randomization and is therefore inherently blinded to treatment allocation. Biostatistical analyses will be conducted on pseudonymized datasets, with treatment allocation unmasked only after database lock, following finalization of the statistical analysis plan.

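### The transrectal versus transperineal comparison of pain and infection is non-randomized and names no adjustment, so route is mixed with centre and anaesthesia to an unknown degree

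*Protocol article*

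**What the plan says.** Secondary objectives (Objectives {7}) include an assessment of transrectal versus transperineal access. Under Outcomes {12} this becomes a comparative secondary outcome for pain and infection: "Compared in terms of pain (VAS score) and infection rates (binary), summarized as mean differences and proportions, assessed within 30 days post-biopsy".

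The Prostate biopsy paragraph (Intervention description {11a}) says that biopsies "will be performed via transrectal or transperineal access under local or general anesthesia". It gives no rule for who receives which route or which anaesthesia, and no time at which either is decided.

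Sequence generation {16a} randomizes men 1:1 between the two biopsy strategies only, and the allocation "will be stratified by study center to ensure balance across recruitment sites". Under Who will be blinded {17a}: "Clinical teams cannot be blinded due to procedural differences between study arms".

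Statistical methods {20a} counts biopsy approach comparisons among the secondary outcomes, to be analyzed descriptively, with inferential methods where suitable. The one model it names for VAS is a repeated-measures model with arm, timepoint and baseline. Methods for additional analyses {20b} lists biopsy approach as a subgroup factor for detection of clinically significant cancer and calls all subgroup analyses exploratory.

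**The concern.** A comparison of routes appears among the trial's between-group outcomes although nothing in the design makes the two route groups comparable. Centres may favour one route, and the mix of local and general anaesthesia may differ by route. Either would move pain or infection without any effect of the route itself. A reader of the results could take the difference as evidence about route, because nothing in the article marks it as observational.

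Timing raises a second matter. Biopsy follows randomization, the teams are not blinded, and Arm B adds 12 systematic cores. If an operator picks the route knowing the arm, arm enters the route contrast. Route would then be a post-allocation variable, and comparing arms within a route for clinically significant cancer would no longer be protected by randomization.

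**Working it through.** The protocol gives no rate, standard deviation, sample size or power for the route comparison, so there is no figure to reproduce. The 477 men per arm are sized for detection of clinically significant cancer and say nothing about route. The check has two parts.

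**1. What the text fixes**

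- Randomized: biopsy strategy. Stratified by: centre. Route and anaesthesia: neither.
- Time at which route is chosen: not stated. The text says neither that it precedes allocation nor that it follows it.
- Stated summary: mean differences and proportions. Adjustment for centre, anaesthesia or arm: none named.
- Only VAS model named: arm, timepoint, baseline. It has no term for route, centre or anaesthesia.

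**2. How far an unadjusted contrast could move with no true route effect**

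All inputs here are assumptions. For one binary confounder, bias = (share in transperineal group − share in transrectal group) × effect of the confounder.

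*Anaesthesia.* Assume general anaesthesia changes VAS by −2 points and is used in 20% of transrectal biopsies.

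| General anaesthesia, transperineal | Calculation | Spurious difference (VAS points) |
|---|---|---|
| 20% | (0.20 − 0.20) × (−2) | 0 |
| 40% | (0.40 − 0.20) × (−2) | −0.4 |
| 60% | (0.60 − 0.20) × (−2) | −0.8 |
| 80% | (0.80 − 0.20) × (−2) | −1.2 |

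*Arm.* If Arm B makes up 60% of one route group and 40% of the other, the bias is 0.60 − 0.40 = 0.2 VAS points per 1-point arm effect; at 70% and 30% it is 0.4. At 50% and 50%, which is expected when route is chosen independently of arm, it is 0.

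*Centre.* Assume each centre uses one route (4 versus 4), 2 × 477 / 8 ≈ 119 men per centre, and a residual SD of 2 points.

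- Variance assumed by an unadjusted test: 2 × 2² / (4 × 119) = 0.0168.
- Actual variance with centre SD s: 0.0168 + 2 × s² / 4.
- For s = 0.2 the actual variance is 0.0168 + 0.0200 = 0.0368. The effective critical value is 1.96 × √(0.0168 / 0.0368) = 1.32, a two-sided error of about 18–19%.
- Simulation of the unadjusted t-test at a nominal 5% (4,000 runs each) gave about 18%, 31% and 49% for s = 0.2, 0.3 and 0.5.

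For infection the same bias formula holds on the risk-difference scale, but the document supplies nothing to put into it.

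**The case against.** The strongest reply is that the outcomes section gives only a metric and a method of aggregation. It never calls the analysis unadjusted, and covariates for a descriptive secondary comparison can properly be left to the analysis plan, which is not shown. The eCRF structure sits in an operations handbook, also not shown, so the needed fields may already exist. The comparison is nowhere called causal, confirmatory or powered, and the subgroup analyses are labelled exploratory. All of this stands, and it limits the point.

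Several stronger readings are tempting, and the documents do not support them:

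- *That the objective measures centre, anaesthesia and arm instead of route.* The text supports only a mixture of unknown degree.
- *That route is chosen after allocation.* The article is silent on this. If route follows centre habit, centre-stratified 1:1 allocation balances the arms within route; arm then does not confound the contrast, and the subgroup by route keeps its randomized comparison.
- *That the trial rests a move to transperineal access on this comparison.* The background section only mentions a possible benefit of that approach and cites outside literature.
- *That the bias is of a known size.* The illustrations use assumed inputs. The assumed 2-point anaesthesia effect may not carry over to a VAS score recorded up to 30 days later.

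One part of the reply fails. Covariates can be chosen in a later analysis plan, but planned route and planned anaesthesia cannot be recovered once the arm is known. The plan need only be final before database lock, projected for October 2030.

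**Conclusion.** The point holds in a limited form. Route is neither randomized nor a stratification factor, nothing in the article says it is set before allocation, and the stated summary names no adjustment. The contrast is therefore observational and open to confounding by centre and anaesthesia. Confounding by arm, and the loss of a baseline subgroup, follow only if route is chosen with knowledge of the arm.

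Size and direction cannot be determined from the document, and the bias may be zero. The illustrations show that modest imbalances could matter; they do not show that such imbalances exist. The co-primary comparisons are unaffected. This is an inexpensive improvement to a secondary outcome, worth making as early in recruitment as possible.

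**What to change.** 1. Add planned route and planned anaesthesia to the eCRF, to be completed before the randomization system releases the arm, unless the operations handbook already provides for this. This records a choice and does not restrict it.
2. In Methods for additional analyses {20b}, define the biopsy-approach subgroup by planned route.
3. In Outcomes {12}, state that the route difference in VAS and infection is estimated with arm, centre and anaesthesia type accounted for, drawing on within-centre information where centres use both routes. If centres use a single route, a model with centre terms cannot separate route from centre, and the result should be descriptive only.
4. Label the result a non-randomized association.

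The cost is two extra fields and wider intervals, with little information about route if most centres use only one. The trial status section puts the planned start of recruitment at 15 April 2026, so any men randomized before the fields are added would lack the planned values.

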**Methods:**

PRIMA is a randomized, prospective, multicenter non-inferiority diagnostic accuracy trial in eight German hospitals. Biopsy-naïve men aged 50–75 years with PSA ≥ 3 ng/ml and/or suspicious DRE undergo mpMRI (PI-RADS v2.1, PI-QUAL v2). Men with PI-RADS 4–5 or PI-RADS 3 with PSA density > 0.15 are randomized 1:1 to TB only (Arm A) or TB + SB (Arm B). Persistent PI-RADS 4–5 lesions with negative biopsy undergo MRI in-bore biopsy.

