#### MR in-bore biopsy

For participants with PI-RADS 4–5 lesions and negative TB or TB + SB, MR in-bore biopsy will be offered after consensus reading. Needle placement will be confirmed in two imaging planes, and 2–4 cores per lesion will be acquired, with additional cores permitted if targeting is inaccurate.

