### Strategies to improve adherence to interventions {11c}

As PRIMA is a diagnostic accuracy trial without therapeutic intervention, adherence is expected to be high. All participants (Arms A and B) benefit from access to high-quality mpMRI and standardized biopsy procedures at experienced centers, which is commonly perceived as advantageous care. All participants receive structured follow-up imaging and, if indicated, MR in-bore biopsy to ensure that csPCa is not missed in either study arm, reducing concerns about randomization.

Adherence will be supported through clear communication, appointment reminders, and direct contact with study nurses. Completion of scheduled procedures will be monitored through the electronic trial database, and adherence metrics will be reviewed in monthly Trial Steering Committee meetings.

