### Plans to promote participant retention and complete follow-up {18b}

Participant retention in PRIMA is supported by clear communication of the clinical relevance of structured imaging follow-up and by scheduling support from study nurses at each site. Reminder systems, including scheduled telephone, electronic or postal notifications, will be used to encourage attendance at follow-up visits, particularly the 30-day safety visit and the 12-month mpMRI assessment. Missed appointments will be actively followed up by site investigators or study nurses to re-schedule assessments where feasible.

If participants discontinue allocated biopsy procedures, routinely collected clinical data—including follow-up MRI results, histopathology reports, adverse events and patient-reported outcomes—will continue to be collected unless consent is formally withdrawn. Reasons for withdrawal or protocol deviation will be documented in the electronic trial database.

For participants lost to follow-up, electronic hospital records may be reviewed to identify biopsy results, MRI findings, or cancer diagnoses when permitted by local data-protection regulations. Participants diagnosed with csPCa (ISUP ≥ 2) will exit the trial and enter guideline-based standard-of-care treatment; data collection until the time of exit remains part of the primary analysis.

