### Methods for additional analyses (e.g., subgroup analyses) {20b}

Pre-specified subgroup analyses will explore whether the effect of targeted biopsy alone versus combined biopsy on the detection proportion of clinically significant prostate cancer (csPCa; ISUP ≥ 2) varies across clinically relevant strata, assessed at index biopsy.

Planned subgroup analyses include:PI-RADS category: PI-RADS 4 vs PI-RADS 5PSA density (PSAD): ≤ 0.15 vs > 0.15–0.20 vs > 0.20Biopsy approach: transrectal vs transperinealProstate volume: < 60 ml vs 60–100 ml vs > 100 mlAge categories: 50–60, 61–70, 71–75 yearsNumber of MRI lesions: single index lesion vs multiple lesionsMRI quality: PI-QUAL 2 vs PI-QUAL 3Follow-up imaging outcome: stable vs up- or downgraded PI-RADS at 12 monthsHistopathology outcome: ISUP 1 only vs no cancer on initial biopsy

Interaction terms will be evaluated using logistic regression models to assess effect modification on the primary endpoint. All subgroup analyses will be exploratory, hypothesis-generating, and interpreted descriptively without correction for multiplicity.

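### The MR in-bore yield outcome includes men with ISUP 1 results, whom the protocol's own trigger for the procedure does not cover

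*Protocol article*

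**What the plan says.** Three places in the protocol article describe the step from index biopsy to MR in-bore biopsy.

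- Intervention description {11a}, MR in-bore biopsy: "For participants with PI-RADS 4–5 lesions and negative TB or TB + SB, MR in-bore biopsy will be offered after consensus reading".
- Abstract, Methods: "Persistent PI-RADS 4–5 lesions with negative biopsy undergo MRI in-bore biopsy".
- Outcomes {12}, Secondary outcomes, MR in-bore biopsy yield: "Defined as detection of csPCa in participants undergoing MR in-bore biopsy", and the definition then covers "MR in-bore biopsy after negative or ISUP 1 results (metric: binary), reported as proportion, assessed within 3 months post-biopsy".

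The adherence section {11c} relies on the procedure as a safeguard without giving a trigger: "All participants receive structured follow-up imaging and, if indicated, MR in-bore biopsy to ensure that csPCa is not missed in either study arm". The subgroup list in {20b} treats two index-biopsy results as different categories: "ISUP 1 only vs no cancer on initial biopsy".

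**The concern.** The rule that sends a man to in-bore biopsy and the outcome that measures its yield should describe the same men, and here they do not. A man with a PI-RADS 5 lesion and an ISUP 1 result falls outside the offer in the intervention section and in the abstract, yet the outcome definition foresees men like him. A site that follows the intervention section will not offer him the procedure. A site that works from the outcome may do so.

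Two things are at stake. One is who is offered a further invasive procedure, and an analysis plan cannot settle that afterwards. The other is what a named secondary outcome measures. The Discussion says the trial will show under which conditions in-bore biopsy is valid and safe when only targeted biopsy is used, and that aim needs those conditions to be stated once and consistently.

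**Working it through.** **1. The three texts side by side**

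| Source | PI-RADS | Index result | Further condition | Wording | Time |
|---|---|---|---|---|---|
| Intervention {11a} | 4–5 | negative | consensus reading | offered | none |
| Abstract | 4–5 | negative | lesion persistent (undefined) | undergo | none |
| Yield outcome {12} | none stated | negative or ISUP 1 | none | undergoing | 3 months |

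They differ in result category, PI-RADS restriction, further condition, and whether the procedure is offered or simply done.

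**2. Does negative include ISUP 1?** The yield outcome lists ISUP 1 beside negative as an alternative, and the subgroup list sets ISUP 1 against no cancer. On the protocol's own usage the two are separate.

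**3. The base of 477 per arm reproduces.** Inputs from Sample size {14}: csPCa 50% in Arm B, true difference −5 points (so 45% in Arm A), margin 13 points, one-sided α = 0.05, power 80%.

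- Unpooled normal approximation: n = (1.645 + 0.842)² × (0.50×0.50 + 0.45×0.55) / (0.13 − 0.05)² = 481 per arm.
- Score test with the null variance at the restricted maximum-likelihood estimates: 477 per arm, power 80.1%, which matches the protocol.
- ISUP 1, 15% against 0.6 × 15% = 9%, 460 per arm, one-sided α = 0.05: power 87.7% against the stated 88%.

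**4. Size of the disputed group.** Each man is classed by his highest grade, so negative = 1 − csPCa − ISUP 1.

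| | Arm A | Arm B |
|---|---|---|
| csPCa | 45% | 50% |
| ISUP 1 | 9% | 15% |
| Negative | 46% | 35% |
| ISUP 1, × 477 | 42.9 | 71.6 |
| Negative, × 477 | 219.4 | 167.0 |
| ISUP 1 share of men without csPCa | 0.09/0.55 = 16.4% | 0.15/0.50 = 30.0% |

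**5. Restriction to PI-RADS 4–5.** The planning mix is 10% PI-RADS 3 with high PSA density, 30% PI-RADS 4 and 20% PI-RADS 5, so PI-RADS 4–5 make up 50/60 = 5/6 of randomized men. Assume the same result mix in every PI-RADS category; the protocol does not give it.

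| Men with PI-RADS 4–5 | Arm A | Arm B |
|---|---|---|
| ISUP 1 | 35.8 | 59.6 |
| Negative only | 182.9 | 139.1 |
| Negative or ISUP 1 | 218.6 | 198.8 |

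If the PI-RADS 4–5 share among these men is anywhere from 75% to 100%, the ISUP 1 group is 32 to 43 men in Arm A and 54 to 72 in Arm B. Admitting ISUP 1 men enlarges the candidate pool by 0.09/0.46 = 20% in Arm A and 0.15/0.35 = 43% in Arm B.

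**The case against.** The strongest reply is that the intervention section is the operative text, the abstract is a condensation, and negative may have been meant as negative for csPCa. On that reading the ISUP 1 conflict disappears. It is possible, but the protocol does not say so, and its usage elsewhere points the other way. It would also leave the PI-RADS restriction and the word *persistent* unreconciled.

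Four stronger readings are tempting, and the documents do not support them.

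- *ISUP 1 men are counted in the yield without being offered the procedure.* The denominator is men who undergo it, so a man who is not offered it is not counted. The defect is a named group with no stated route into it.
- *The timing contradicts itself, because persistence can only be seen on the 12-month MRI.* The retention section {18b} does stress follow-up visits, "particularly the 30-day safety visit and the 12-month mpMRI assessment", and no other repeat MRI has a stated time. But only the yield outcome gives a time for in-bore biopsy. *Persistent* could mean still suspicious at consensus reading. The caption of Fig. 1 lists in-bore biopsy before the 30-day visit, which fits an early procedure. The participant timeline {13} makes repeat MRI depend on the biopsy result and points to a figure that is not shown. The word needs defining; a clash is not established.
- *The unclear trigger biases a comparison between arms.* No comparison of yield by arm is stated. Each text applies one rule to both arms, and randomization is stratified by center, so a site's reading falls on both its arms. The pools differ under either rule, and the gap is larger under the negative-only rule (183 against 139, a gap of 44) than with ISUP 1 added (219 against 199, a gap of 20). What stands is narrower: if ISUP 1 men are escalated, their share of the pool is expected to differ by arm, and clinical teams know the allocation when they decide.
- *The main conclusion is at risk.* Both co-primary outcomes are assessed at index biopsy, so in-bore results do not enter them.

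It is also fair to say that tables by prior result usually belong in an analysis plan. The trigger does not.

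**Conclusion.** The inconsistency is real and limited to a secondary outcome. The yield definition includes men with ISUP 1 results and sets no PI-RADS restriction, whereas the two texts that trigger the procedure name only negative biopsies with PI-RADS 4–5 lesions, one of them with an undefined persistence condition. Under the planning rates the disputed group is about 43 men in Arm A and 72 in Arm B, or about 36 and 60 with PI-RADS 4–5. These counts rest on 477 analyzed men per arm, on the protocol's assumed detection rates, and, for the restricted pair, on an equal result mix across PI-RADS categories. They are expected candidates, not men known to be mishandled. The non-inferiority test, the ISUP 1 test and the sample size are untouched. It is worth correcting because it governs who is offered an invasive procedure and what a named outcome means.

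**What to change.** Reconcile the abstract, the MR in-bore biopsy section and the yield outcome to one trigger, applied identically in both arms. It should state the index-biopsy result category (and whether negative includes ISUP 1), the PI-RADS restriction, what *persistent* means or that it is dropped, and whether the procedure is offered or required. Then make the yield population and the 3-month window match that trigger. Which clinical rule is right is for the investigators.

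If ISUP 1 men are included, tabulate the yield by prior result (negative, ISUP 1), because that mix is expected to differ by arm.

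The cost is a few sentences of protocol text and, in that case, one table. No participants are added, and no procedures beyond those that one of the passages already foresees. The article reports that nobody had been enrolled at submission and that recruitment was planned from 15 April 2026, so the change is cheapest now. Men already managed under different readings could not be re-sorted later.
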